## Abstract

**Background:**

Clinical practice guidelines for the treatment of major depressive disorder (MDD) recommend antidepressants for patients with moderate-severe depression and active monitoring for patients with mild-moderate symptoms. The feasibility and efficiency of active monitoring has not been proven conclusively. The aim of this study is to evaluate the cost-effectiveness of active monitoring in comparison to antidepressants for primary care patients with mild-moderate MDD.

**Methods/Design:**

This is a 12-month follow-up multicenter observational prospective controlled trial. Patients are enrolled in 12 primary care centers in Barcelona (Spain). Eligible patients are adults (≥18 years-old) with a new episode of MDD that sign a written consent to participate. This is a naturalistic study in which general practitioners (GPs) use their professional judgment to allocate patients into active monitoring or antidepressants groups. GPs treat the patients following their clinical criteria. At baseline, GPs complete a questionnaire (sociodemographic/job characteristics, training, attitude towards depression, interest on mental health and participation in communication groups). Patients’ measurements take place at baseline and after six and 12 months. Main outcome measures include severity of depression (PHQ-9), health-related quality of life (EuroQol-5D) and use of healthcare and social care services (Client Service Receipt Inventory). Secondary outcomes include diagnosis of MDD according to DSM-IV diagnostic criteria (SCID-I), disability (WHO-DAS), anxiety (BAI), comorbidities, medication side-effects and beliefs about medicines (BMQ).

The analysis will be done according to the intention to treat analysis. Missing data will be imputed using multiple imputation by chained equations. To minimize the bias resulting from the lack of randomization, a propensity score will be used. Incremental effects and costs between groups will be modelled in each of the imputed databases using multivariate generalized linear models and then combined as per Rubin’s rules. Propensity scores will be used to adjust the models. Incremental cost-effectiveness ratios will be calculated by dividing the difference in costs between groups by the difference in effects. To deal with the uncertainty, resampling techniques with bootstrapping will be used and cost-effectiveness planes and cost-effectiveness acceptability curves will be constructed. A series of sensitivity analyses will be performed.

**Discussion:**

Given the high burden and costs generated by depressive disorder, it is important that general practitioners treat major depression efficiently. Recent evidence has suggested that antidepressants have low benefits for patients with mild to moderate major depression. For such cases of depression, active monitoring exists as a treatment option, but it is not without difficulties for implementation and its effectiveness and efficiency have not been demonstrated conclusively. The results of the study will provide information on which is the most efficient approach to treat patients with mild to moderate major depression in primary care.

**Trial registration:**

ClinicalTrials.gov: NCT02245373

## Background

Major depressive disorder (MDD) generates high expenditure that is caused largely by its high prevalence, its recurrence and chronicity and because it usually affects young people of working age [1,2]. The social cost of this mental disorder is also very high, given the risk of suicide and the serious negative impacts in social, occupational and family situations [3]. From the work carried out by Goldberg and Huxley in the eighties, it is widely recognized that major depression is mainly treated at the primary care level [4]. More recent studies indicate that 10% to 16% of primary care patients fulfill criteria for a diagnosis of MDD [5,6]. It is therefore important that general practitioners (GPs) be capable of detecting and treating MDD using evidence-based medicine and taking the particularities of the primary level of care into account.

Psychotropic drugs, mostly antidepressants and anxiolytics, are highly prescribed in primary care in our setting as they are the standard treatment for MDD. About 70% of patients with a mood disorder receive psychotropic drugs in Catalan primary care [7]. Moreover, almost 25% of patients who do not fulfil criteria for a mood or anxiety disorder are also prescribed a psychotropic drug [7]. This percentage could include patients with minor depression or psychological distress that the GP misdiagnosed [8,9]. A review showed that benefits of antidepressants depend on the severity of the depressive episode, which may be minimal in patients with mild to moderate symptoms [10]. Another review showed that brief psychological therapy (brief cognitive behavioral therapy (CBT), counselling and problem solving therapy) were effective treatments in primary care for patients with anxiety, depression and mixed mental health problems [11]. The recommendations of the clinical practice guidelines for the treatment of MDD vary according to the severity of the case. The guidelines recommend medication for patients with moderate and severe depression and active monitoring (or watchful waiting) and referral for further assessment and interventions for those with mild to moderate symptoms [12,13].

Active monitoring has been described as a decision “between the clinician and the patient to not treat the condition and to intermittently reassess its status along some rational time course in follow-up” [14]. According to the Catalan guideline [13], for patients receiving active monitoring, the GP should monitor the patient within 15 days of the first visit. Other recommendations are to accompany closed monitoring with low intensity psychosocial therapy (e.g. problem-solving techniques, counselling or brief CBT), individual guided self-help programs based on CBT or structured and supervised exercise programs of moderate intensity. The guidelines only recommend the use of antidepressants in mild major depression if the patients have a history of moderate or severe episodes of depression or if they have other medical conditions or associated comorbidities.

Despite being recommended in guidelines, the effectiveness of active monitoring has not been proven conclusively. There has been a study showing a low likelihood of spontaneous remission in minor depression following a one-month active monitoring period in primary care. However, the same study showed that engaging in regular pleasant activities conferred an advantage to remission in minor depression.. The study recommended the use of feasible interventions that promote activity and decrease avoidant coping styles in primary care [14]. Furthermore, an economic evaluation of usual GP care with or without antidepressant medication for patients with minor or mild-major depression observed no differences in cost-effectiveness between the two treatment strategies, recommendeding that GPs sparingly prescribe antidepressants to mildly depressed patients [15]. On the contrary, in older primary care patients with dysthymia and minor depression, a problem-solving behavioral based psychotherapy in primary care showed smaller benefits for depressive symptoms than paroxetine [16]. More recently, the THREAD study compared selective serotonin reuptake inhibitors (SSRIs) plus supportive care versus supportive care alone for mild to moderate depression with somatic symptoms in primary care [17]. The study showed that adding an antidepressant was more cost-effective than supportive care alone.

An additional problem regarding active monitoring is the lack of consensus on what is the best strategy for implementation and how to overcome the lack of adherence to recommendations. A study examining the factors associated with GPs’ choice of watchful waiting to care management of depression showed barriers that included the clinicians lack of knowledge on psychotherapy and the lack of availability of mental health professionals for referral [18]. In order to choose watchful waiting, GPs may be able to schedule follow-up appointments with the patient and perform low intensity psychosocial interventions or have available referral services for the patient. However, GPs do not routinely receive training in psychological therapy and the adequate number of follow-up sessions (one within the first 15 days and from six to eight during the 10–12 weeks following the diagnosis [13]) can be unrealistic given the existent burden in primary care. This is illustrated by the study by Hegel and colleagues, where the proportion of patients that received at least one contact with the GP during the first month of watchful waiting was of only 21% [14].

It is still necessary to show whether non-pharmacological interventions in mild-moderate major depression can be a feasible and cost-effective alternative compared to pharmacological interventions in actual practice primary care. The aim of this study is to evaluate the cost-effectiveness of active monitoring in comparison to the use of antidepressants for the treatment of mild to moderate MDD in primary care usual practice in a 12-month non-randomized controlled trial.

## Methods

We followed the SPIRIT statement for reporting trial protocols [19]. This is the first published version of the protocol.

### Study design

This is a 12 month follow-up multicenter observational prospective controlled trial comparing patients that receive antidepressant drugs with those who do not. The study was approved by the Clinical Research Ethics Commitee of the Sant Joan de Déu Foundation (CEIC Fundació SJD; Reference Number: EPA-24-12) and the Clinical Research Ethics Commitee of The Jordi Gol i Gurina Foundation (CEIC IDIAP; Reference Number: 5013 – 002).

### Study setting and GP enrolment

GP enrolment was conducted six months before patient recruitment. GPs from the province of Barcelona were invited to participate. The University Institute in Primary Care Research Jordi Gol (IDIAP Jordi Gol), which gives technical support to every professional that works in Primary Care in the Catalan Public Health System, spread the invitation to participate in the study to all the GPs from the province of Barcelona. Furthermore, the research team contacted the Primary Care Centers with whom they had worked in previous research studies to invite them to participate.

The study is conducted in 12 primary care centers in the province of Barcelona (Spain). The participating centers have between six and 17 primary care teams (each of them consisting of a GP and a nurse) and attend to a population of 250,000 to 350,000 inhabitants. Sixty-eight GPs participated in the recruitment of patients for the study.

Prior to the study, GPs received a three hour-training on the study protocol, diagnostic criteria for depression, and national guidelines for the treatment (pharmacological and non-pharmacological) of MDD in primary care, divided into two 1.5-hour sessions. Session 1: Diagnosis and non-pharmacological treatment for MDD (active monitoring, sleep hygiene, counseling, frequency of follow-up visits, health education and low intensity psychological therapies); and Session 2: pharmacological treatment of MDD. During the study, a monthly newsletter is sent to the participating GPs to remind them of the topics presented in the training seminars and to inform them about the study progress.

At the beginning of the study, the GPs completed a questionnaire collecting the following variables: sociodemographic characteristics, job characteristics, training, attitude towards depression, interest on mental health and participation in communication groups [20].

### Eligibility criteria and recruitment

Eligible patients are adults (≥18 years-old) who receive a diagnosis for a new episode of MDD. The following patients are excluded: those that have taken an antidepressant medication in the previous 60 days; those presenting psychotic or bipolar disorders or on antipsychotics, lithium or antiepileptics in the previous six months; those with history of drug abuse or dependency; those with cognitive impairment that prevents an assessment interview; and those who refuse to give signed consent to participate.

GPs recruit patients for the study from their daily list of patients attending the practice until they reach five patients for each group (active monitoring or pharmacological treatment). Maximum recruiting time is 12 months. For patients meeting the inclusion criteria, GPs inform them of the study’s aim and procedures during the medical visit, where a written informed consent is also obtained. GPs then refer patients for their first assessment appointment.

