**Figure 1 Fig1:**
[figure not shown]
**Schedule of enrolment, interventions and assessments.** PHQ-9 = Patient Health Questionnaire; CSRI = Client Service Receipt Inventory; BMQ = Beliefs about Medicines Questionnaire; SCID-I = Structured Clinical Interview for DSM Disorders; BIPQ = Brief Illness Perception Questionnaire; WHO-DAS 2.0 = World Health Organization Disability Assessment Schedule; BAI = Beck Anxiety Inventory; MAQ = Medication Adherence Questionnaire.

Costs are collected from a societal perspective. Use of health care resources and lost productivity are assessed using the Client Service Receipt Inventory (CSRI) [22] with a recall period of 12 months at baseline and six months at point two and close-out. We collect information on productivity losses, health tests, hospital care (emergency visits and stays), secondary care (visits to psychologists, psychiatrist and other specialists), primary care (visits to GP and nurse), medication use and social care services (visits to social worker). Information on the use of psychotropic medicines (active principle, dose and units supplied) is also collected from computerized pharmacy records.

The unit costs of public healthcare services are obtained from the Official Bulletin of the Catalan Government. Costs of privately funded services are obtained from published tariffs. The mean price per milligram of active principle is calculated using the prices of the generic versions of all the presentations as reported in the Spanish Vademecum. Productivity losses will be calculated based on the human capital approach using information on the minimum and average daily wage in Spain (INE) [23].

Changes in the severity of depression are assessed using the Patient Health Questionnaire 9-item depression module (PHQ-9) [24-26]. The PHQ-9 is a nine-item scale with items scored from 0 (not at all) to 3 (nearly every day) on nine symptoms of depression. Summed scores range from 0 (no depressive symptoms) to 27 (all symptoms occurring daily). Summed scores of 20 to 27 correspond to severe symptoms; 15 to 19 to moderately severe; 10 to 14 to moderate symptoms; 5 to 9 to mild symptoms; and 0 to 4 to minimal symptoms.

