### Sensitivity analyses

At minimum, the following sensitivity analyses will be performed: 1) an analysis from the healthcare perspective; 2) a per protocol analysis; 3) an analysis using the mean average salary instead of the minimum average salary for productivity losses; 4) an analysis not adjusted for the propensity score; 5) an analysis including only the patients that fulfill DSM-IV criteria for MDD.

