## Discussion

The results of this study will provide evidence about whether active monitoring in mild-moderate MDD can be a feasible and cost-effective alternative to pharmacological interventions in actual practice primary care. Although clinical practice guidelines recommend active monitoring, evidence of its effectiveness and efficiency is scarce and contradictory. This study will improve knowledge on active monitoring efficiency and, as far as is known, it will be the first study on this topic to be conducted in Spain. If non-pharmacological interventions would prove to be more cost-effective than pharmacological ones, this would show that preventing the use of antidepressants in patients with mild-moderate MDD could save the health care system money and protect patients from side-effects of non-necessary drugs.

The study has a series of limitations that must be considered. The naturalistic nature of the study implies the use of wide inclusion criteria and non-randomized group assignment, which increase the external validity of the results. However, wide inclusion criteria can increase the inter-subject variability and reduce the ability to detect differences. It is more likely for the GP to allocate patients presenting with mild depression to the active monitoring group than to the pharmacological treatment group. Conversely, for patients with moderate-severe depression, GPs might be more likely to choose pharmacological options than active monitoring. Propensity score techniques will be used to try to minimize the impact of this bias in the results of the study.

One limitation of the study is the GP selection. The group of GPs that decided to participate in the study could have a greater interest in mental health. This might include specific attitudes of those GPs when facing physiological problems in primary care and might not represent average GP behavior. Along these lines, it is possible in this study that GPs enroll patients that they think that will be more willing to participate and remain in the study. Also, all the health centers are located in the same health area, so the intervention can be biased for specific practices associated to local culture or characteristics of the health system.

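### The aim and planned conclusion are for mild-moderate MDD, but neither eligibility nor any listed analysis limits severity, so the pooled estimate need not answer the stated question

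*Protocol article*

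**What the plan says.** All references are to the protocol article.

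- **Aim.** The Abstract and the end of the Background give the target as cost-effectiveness "for the treatment of mild to moderate MDD in primary care usual practice in a 12-month non-randomized controlled trial".
- **Planned conclusion.** The Discussion says that the results will show "whether active monitoring in mild-moderate MDD can be a feasible and cost-effective alternative to pharmacological interventions in actual practice primary care". It goes on to possible savings from avoiding antidepressants in that same group.
- **Eligibility.** Under Eligibility criteria and recruitment: "Eligible patients are adults (≥18 years-old) who receive a diagnosis for a new episode of MDD". The exclusions cover recent treatment ("those that have taken an antidepressant medication in the previous 60 days"), psychotic or bipolar disorder and related drugs, drug abuse, cognitive impairment and refusal of consent. None is a limit on depression severity.
- **Expected case mix.** The Discussion on allocation: "Conversely, for patients with moderate-severe depression, GPs might be more likely to choose pharmacological options than active monitoring".
- **Severity as a modifier.** The Background reports a review in which "benefits of antidepressants depend on the severity of the depressive episode, which may be minimal in patients with mild to moderate symptoms".
- **Analysis set.** Statistical analysis includes every patient in the group allocated.
- **Sensitivity analyses.** Five are listed as a minimum. The only one that restricts by clinical status is "5) an analysis including only the patients that fulfill DSM-IV criteria for MDD".
- **Severity scale.** Outcomes and participant timeline gives PHQ-9 bands: "Summed scores of 20 to 27 correspond to severe symptoms; 15 to 19 to moderately severe; 10 to 14 to moderate symptoms", with 5 to 9 mild and 0 to 4 minimal.

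**The concern.** The question is asked about one population and the data come from a wider one. Severity is also the feature on which the Background bases its case: both the cited drug benefit and the guideline recommendations change with it. If the difference between strategies varies with severity, an average over all enrolled patients is not the difference in mild-moderate disease, however well the groups are balanced.

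Followed as written, the study could report a result for all GP-diagnosed new episodes as evidence about mild-moderate MDD and attach the Discussion's policy message to it. The text names no analysis that would show whether the two agree.

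**Working it through.** No stated figure is in dispute. The 150 per arm under Sample size rests on previous experience, with no significance level, power, effect or standard deviation, so there is nothing to reproduce. The point does not depend on it. The check is one of consistency, followed by illustrations under stated assumptions.

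**1. Population at each stage.**

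| Stage | Population |
|---|---|
| Aim (Abstract, Background) | mild-moderate MDD |
| Eligibility | any GP-diagnosed new MDD episode |
| Analysis set | all allocated patients |
| Sensitivity analysis 5 | DSM-IV MDD, any severity |
| Conclusion (Discussion) | mild-moderate MDD |

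Sensitivity analysis 5 removes patients without confirmed MDD and keeps severe ones, so it does not recover the target population.

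**2. Where severity enters the analysis.** Baseline severity is a candidate variable for the propensity score, and baseline clinical variables may be tested as adjustment variables in the cost and effect models. Both uses address confounding. Neither defines the severity mix to which the difference applies.

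**3. Possible gap.** Let w be the weight in the pooled estimate of patients above the mild-moderate range, and g the amount by which their PHQ-9 effect differs from that of the others.

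Pooled effect − mild-moderate effect = w × g

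Neither w nor g is in the document. Assuming w = 0.1 to 0.5 and g = 1 to 3 points:

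- smallest: 0.1 × 1 = 0.1 point
- largest: 0.5 × 3 = 1.5 points

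The sign is that of g, which is also unknown.

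**4. The weight need not equal the share.** In a linear model with a single group effect, a stratum counts roughly as share × p(1 − p), where p is its proportion on active monitoring. Assume equal arms and 40% of patients above the range.

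- If 10% of those are on active monitoring, then p in the rest is (0.50 − 0.40 × 0.10)/0.60 = 0.767. The products are 0.40 × 0.10 × 0.90 = 0.036 and 0.60 × 0.767 × 0.233 = 0.107. The weight is 0.036/(0.036 + 0.107) = about 25%.
- If 5% are on active monitoring, then p in the rest is (0.50 − 0.40 × 0.05)/0.60 = 0.80. The products are 0.019 and 0.096, and the weight is 0.019/0.115 = about 17%.

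With g = 2 to 3 points, weighting by the 40% share gives 0.8 to 1.2 points. The 25% weight gives 0.50 to 0.75, and the 17% weight about 0.33 to 0.50. Poor overlap therefore shrinks the gap but leaves an estimate for an unstated severity mix. Other link functions or standardisation would give other weights.

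**5. Precision cost of restricting.** Assume two-sided 5% significance and 80% power (neither is in the document). The detectable standardised difference is (1.960 + 0.842) × √(1/n₁ + 1/n₂).

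| Assumed share above PHQ-9 14 (monitoring / medication) | Patients left | Detectable difference (SD) |
|---|---|---|
| none removed | 150 / 150 | 0.323 |
| 5% / 20% | 142 / 120 | 0.347 |
| 10% / 30% | 135 / 105 | 0.365 |
| 20% / 50% | 120 / 75 | 0.412 |
| 30% / 60% | 105 / 60 | 0.453 |

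Also leaving out scores of 0 to 4 would reduce the numbers further.

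**The case against.** The best defence is that the study is openly naturalistic with wide criteria, that baseline severity is a candidate for the propensity score, and that the sensitivity list is only a minimum. Interaction or subgroup terms may also sit in an analysis plan that is not shown. Part of this stands: the article does not rule out an interaction, and the absence of one is not in itself a fault. What remains is that the article states the aim, eligibility, analysis set and conclusion, and these do not agree. The Discussion treats wide criteria as a matter of variability and external validity, and severity as allocation bias. It does not discuss the mismatch with the aim.

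A reader might go further in three ways that the document does not support.

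- **That severe patients are concentrated in the medication group and tilt the result toward drugs.** The Discussion says only that GPs might lean that way for moderate-severe patients, a term that overlaps the target's moderate stratum. The exclusion of psychotic disorders and antipsychotic use may remove some severe cases.
- **That there is no drug effect in mild-moderate disease, so any pooled benefit is wrongly attributed.** The Background's review says that the benefit may be minimal. The Background also cites a primary care trial in mild to moderate depression with somatic symptoms, in which adding an SSRI was more cost-effective than supportive care alone. Neither source settles how costs, QALYs or 12-month PHQ-9 differ by severity in this comparison.
- **That the primary population must become PHQ-9 of 14 or less.** That cut also takes in the minimal band, and the article never defines mild-moderate MDD by PHQ-9. Moreover, GPs record allocation and any prescription at inclusion and then refer the patient for the first assessment, so the baseline score may follow the treatment decision.

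**Conclusion.** The mismatch stands on the text, and nothing in the article resolves it. The aim and conclusion are for mild-moderate MDD, while the enrolled and analysed population is any GP-diagnosed new episode. A pooled estimate, even if well adjusted, need not be the mild-moderate effect.

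Whether it differs, by how much and in which direction cannot be known from the document. The 0.1 to 1.5 PHQ-9 points above come entirely from assumed weights and assumed effect differences, and they demonstrate no bias. No corresponding figure can be given for costs or QALYs. This should be fixed, because it determines what the study may conclude. It does not invalidate the full-sample analysis.

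**What to change.** Keep the full sample and, under Incremental cost-effectiveness ratios calculation and Sensitivity analyses, prespecify one analysis to support the mild-moderate conclusion:

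- a restriction to baseline PHQ-9 of 5 to 14, the article's own mild and moderate bands, stating how scores of 0 to 4 are handled; or
- full-sample models with a group × baseline PHQ-9 term, with costs, QALYs and PHQ-9 standardised to that range.

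In either case, report propensity overlap by severity band, and state that baseline PHQ-9 may have been taken after the GP's allocation, with the interval between the two.

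If neither analysis is wanted, reword the aim and the conclusion to GP-diagnosed new MDD episodes of any severity.

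No new data are needed, since PHQ-9 is already measured at baseline. The price of the restricted analysis is fewer patients and wider intervals: under the assumptions above, the detectable difference rises from 0.323 to between 0.347 and 0.453 SD. The interaction model keeps all patients but depends on the assumed form of the severity relation. Rewording costs no precision but gives up the specific mild-moderate claim.
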